## Abstract

**Background:**

A caesarean section (CS) can cause a defect or disruption of the myometrium at the site of the uterine scar, called a niche. In recent years, an association between a niche and postmenstrual spotting after a CS has been demonstrated. Hysteroscopic resection of these niches is thought to reduce spotting and menstrual pain. However, there are no randomised trials assessing the effectiveness of a hysteroscopic niche resection.

**Methods/Design:**

We planned a multicentre randomised trial comparing hysteroscopic niche resection to no intervention. We study women with postmenstrual spotting after a CS and a niche with a residual myometrium of at least 3 mm during sonohysterography. After informed consent is obtained, eligible women will be randomly allocated to hysteroscopic resection of the niche or expectant management for 6 months.

The primary outcome is the number of days with postmenstrual spotting during one menstrual cycle 6 months after randomisation. Secondary outcomes are menstrual characteristics, menstruation related pain and experienced discomfort due to spotting or menstrual pain, quality of life, patient satisfaction, sexual function, urological symptoms, medical consultations, medication use, complications, lost productivity and medical costs. Measurements will be performed at baseline and at 3 and 6 months after randomisation. A cost-effectiveness analysis will be performed from a societal perspective at 6 months after randomisation.

**Discussion:**

This trial will provide insight in the (cost)effectiveness of hysteroscopic resection of a niche versus expectant management in women who have postmenstrual spotting and a niche with sufficient residual myometrium to perform a hysteroscopic niche resection.

**Trial registration:**

Dutch Trial Register NTR3269. Registered 1 February 2012. ZonMw Grant number 80-82305-97-12030

## Background

Caesarean section (CS) rates are rising globally. In the UK the CS rate increased from 12 to 29 % between 1990 and 2008 [1]. In the United States, one in three women delivered by CS in 2011 [1, 2], whereas in China the rates have even risen from 2 % in 1985 to 36–58 % in 2010 [3] The strongest increase was seen in Brazil from 15 % in 1970 to even 80 % in the private sector in 2004 [4]. This increasing CS rate has stimulated an interest in the potential long-term morbidity of CS scars.

BijdeVaate et al. and van der Voet et al. reported a disruption of the myometrium in the uterine scar of a CS seen with saline or gel infusion sonography in approximately 60 % of women who had undergone a CS [5, 6]. Such a disruption or “defect” is called a niche (Fig. 1) [7]. Studies reported sonohysterography to be the most accurate method to identify and measure a niche [5, 6, 8]. Small niches, that are also reported to be associated with bleeding symptoms, can be missed using transvaginal sonography without contrast [5, 6].

**Fig. 1 Fig1:**
[figure not shown]
Sonohysterographic visualisation of a niche. The arrow indicates a disruption of the myometrium in the anterior wall of the uterus over a distance of approximately 15 mm

Prolonged menstrual bleeding and postmenstrual spotting are associated with a niche [5, 6, 9–13]. Two independent cohort studies reported that approximately 30 % of women with a niche experience postmenstrual spotting of more than 2 days versus approximately 15 % of women without a niche after CS [5, 6].

The etiology of niche related postmenstrual spotting and pain has not been fully elucidated. They are thought to be caused by retention of menstrual blood in a niche, which is intermittently expelled after the majority of the menstruation has ceased [11, 14–16]. Blood can also accumulate, if fibrotic tissue in the myometrium at the site of the caesarean scar may impair normal contractions and as a consequence the drainage of menstrual flow [11]. Additionally, newly formed fragile vessels in the niche may also attribute to the accumulation of blood or fluid in the niche or uterine cavity due to a constant low production of in situ leakage of blood and fluid. This is supported by the presence of free blood cells in the endometrial stroma, suggesting recent haemorrhage [17] and hysteroscopic evaluations where small vessels in the majority of patients are seen (Fig. 2) [15, 18–23].

**Fig. 2 Fig2:**
[figure not shown]
Niche surface during hysteroscopic evaluation of proximal part of the niche, several small vessels that easily bleed can be visualised

A few studies reported that niche related menstrual bleeding disorders or cyclic pain do often not respond to hormonal therapies, however some comments can be made concerning the methodology of these studies [22, 24]. Some authors have recommended hysterectomy as a treatment for niche related bleeding complaints, but the exact number of patients undergoing a hysterectomy due to niche related bleeding disorders is yet unknown [11, 14, 25]. It is expected that niche related symptoms are associated to considerable direct and indirect costs, taking into account medical consultation, therapy (including hysterectomy) and absence from work.

Since many reports identified an association between niches and menstrual bleeding disorders after CS [5, 6, 9, 12, 13] several surgical therapies i.e. laparoscopic or hysteroscopic nicheresection or (laparoscopic assisted) vaginal niche repair, have been developed [26]. Of these treatments, hysteroscopic resection of the niche is the least invasive one. Resecting the distal rim aims at improving outflow of menstrual blood. Concurrently superficial coagulation of vessels in the niche aims at reducing blood loss from these fragile vessels.

So far only a few studies reported on a hysteroscopic resection of the niche with coagulation of the niche surface [16, 17, 20–24]. These procedures were reported to improve abnormal blood loss in 87 %, improve pain complaints in 97 % of the cases and no complications occurred [26]. The reduction in spotting days after the procedure compared to baseline was reported in three studies, mean reduction in spotting varied from 2 to 4 days [18, 21, 27].

Thus reported outcomes are promising. However, the methodological quality of these studies is low. Follow-up or validated tools to measure outcomes such as blood loss or quality of life are mostly not reported, most studies are case series or retrospective cohorts and adequately powered prospective comparative studies are lacking [26]. In addition, none of the studies evaluated the effect of hysteroscopic niche resection on quality of life, sexual function, recovery or cost. Before hysteroscopic niche resection is implemented in women that suffer from postmenstrual spotting based on a niche, better assessment of the effectiveness of the treatment is needed.

In view of these arguments, we designed a randomised controlled trial to evaluate the (cost) effectiveness of a hysteroscopic niche resection.

## Methods/Design

### Design

The study is a multicentre randomised controlled superiority trial and will be performed in hospitals that collaborate within the Dutch Consortium for Studies in Women’s Health and Reproduction. Participating centres can be district, teaching or university hospitals. The hospitals are selected based on the presence of extensive experience of their gynaecologists in advanced hysteroscopic procedures, such as hysteroscopic resections of large submucosal fibroids. Gynaecologists will be additionally trained in their centre in the measurement of a niche and in performing a hysteroscopic niche resection by one of the experienced gynaecologists that performed niche resections in a previous pilot study ([name], [name] or [name]).

One of the experienced gynaecologists will be present during the first hysteroscopic niche resection and if needed also during following hysteroscopic niche resections in each centre.

### Participants/eligibility criteria

We will study women who developed postmenstrual spotting after a CS, and in whom sonohysterography has shown a niche of at least 2 mm depth and a residual myometrium of at least 3 mm. Postmenstrual spotting is defined as two or more days of intermenstrual spotting or as two or more days of brownish discharge immediately after the menstrual period in case the total period of the menstrual bleeding exceeds 7 days, if the period is shorter then 7 days the brownish discharge is considered to be normal.

In these women, saline or gel sonohysterography (SIS or GIS) will be performed as part of routine diagnostic work-up for identification of the origin of the bleeding. Exclusion criteria are a residual myometrium less than 3 mm at sonohysterography, age below 18 years, pregnancy, a (suspected) malignancy, contra-indications for spinal of general anaesthesia, uterine or cervical polyps, submucosal fibroids, atypical endometrial cells, cervical dysplasia, cervical or pelvic infection, hydrosalpinx that communicates with the uterus or an irregular cycle (>35 days or intercycle variation of 2 weeks or more).

### Procedures, recruitment, randomisation, collection of baseline data

Before study entry, the niche will be measured with transvaginal sonography and saline or gel infusion sonography in the sagittal plane where the largest niche is visible and in the transversal plane where the niche is largest i.e. with the thinnest residual myometrium. Depth, residual myometrium and the shape of the niche will be registered (see Fig. 3a, b and c). For inclusion, a niche needs to be at least 2 mm deep and the residual myometrium should not be less than 3 mm in one of the planes during SIS or GIS, given the anticipated risk on perforation or bladder injuries with a smaller residual myometrium. Position of the uterus, fluid in the uterine cavity and/or niche, abnormalities of the fallopian tubes and/or ovaries are also registered. A cervical PAP-smear will be obtained to ensure the absence of cervical dysplasia.

**Fig. 3 Fig3:**
[figure not shown]
Niche measurement during sonohysterography in the sagittal plane (**a**), transversal plane (**b**) with the thinnest residual myometrium and niche shape will be registered in both planes (**c**). **a** Measuring a niche in the sagittal plane. Schematic drawing demonstrating how to measure a niche in the sagittal plane. The depth of the niche is measured from the usual limit of the uterine cavity until the apex of the niche (1), the residual myometrium from the apex of the niche until the serosa (2). **a** is an adapted figure of the one that was published by Bij de Vaate et al. 2011 [5]. **b** Measuring a niche in the transversal plane. Schematic drawing demonstrating how to measure a niche in the transversal plane. The depth of the niche is measured from the usual limit of the uterine cavity until the apex of the niche (1) and the residual myometrium from the apex of the niche until the serosa (2). **c** Niche shape. Schematic diagram demonstrating classification used to assess niche shape as published by Bij de Vaate et al. 2011: triangle, semicircle, rectangle, circle, droplet and inclusion cysts [5]

Eligible women will be informed about the study by one of the gynaecologists, residents or research nurse in the participating centre. The informed consent form must be signed before involvement in any study related activity. After written informed consent is obtained, eligible women will be randomly allocated to hysteroscopic resection (experimental intervention) or no intervention (control). Randomisation will be performed by using ALEA, an online randomisation program, managed by the Clinical Research Unit in the Academic Medical Centre in Amsterdam, with the use of permuted blocks with a random block size of 2 to 4 patients per block, stratified for participating centres.

At the time of randomisation, baseline, obstetric and medical history are reported in the case report file. The patient will receive digital online secured questionnaires at baseline, 3 and 6 months after randomisation about their menstrual pattern and uterine bleeding, will complete a validated menstrual bleeding score chart [28], validated questions to report on quality of life (SF-36: Short Form 36 [29, 30] and Euro-QOL 5D: Euro Quality of Life in 5 dimensions [31]), sexual function (FSFI: Female Sexual Function Index) [32] and absence from work (HLQ: Health and Labour [33]). Medical consultation, medication use and received additional therapies will be registered at the same timepoints in an online diary. Any received additional therapy will be registered in the case report file.

Three months after randomisation all patients will undergo transvaginal sonography to register all niche features as at baseline. Patients will be motivated to undergo a SIS or GIS, however saline or gel instillation will be omitted in case patients experienced too much discomfort during this procedure at baseline (see Fig. 4 for the flowchart).

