#### Statistical analysis

Analyses will be performed according to intention-to-treat principle and additionally by per protocol analysis. All tests will be performed two sided and a *p*-value <0.05 will be considered as statistically significant. The difference between the two groups at 6 months follow-up regarding total number of postmenstrual spotting days during one menstrual cycle, duration of menstrual bleeding, number of days of brownish discharge, menstrual pain, experienced discomfort of spotting and of menstrual pain, SF-36 domain scores and EuroQol will be analysed using linear regression analyses, adjusted for relevant baseline values. Potentially relevant confounders are additional hormonal therapy, smoking and use of anticoagulation. Logistic regression analysis will be used to evaluate the existence of (midcycle) intra-uterine fluid. To compare satisfaction with treatment, reported on a 0–5 point scale at six months a (multinominal) logistic regression analysis will be used.

We have planned four subgroup analyses, for:

1) Total days of spotting at the end of the menstruation and intermenstrual spotting >25^th^ centile versus ≤ 25^th^ centile and >75^th^ centile or ≤75^th^ centile at baseline;

2) Number of days postmenstrual spotting >25^th^ centile versus ≤2 25^th^ centile and >75^th^ centile versus ≤75^th^ centile at baseline;

3) Small versus larger niches (using a cut-off of residual myometrium of 3 and 5 mm and <50 % of total myometrial thickness (sum of RM and niche depth) at baseline;

4) A history of 1 versus more than 1 CS at baseline.

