### Strengths and limitations

This trial is the first randomised controlled trial that will provide evidence for the (cost) effectiveness of hysteroscopic resection of a niche versus expectant management in women with niche related postmenstrual spotting.

The HysNiche study is adequately powered. Randomisation is performed with the use of allocation concealment through a webbased randomisation program, which reduces the chance for bias. The study is not blinded for the patient, which could possibly effect reported outcomes by the patient. We found it ethically not justified to ask patients to undergo a hysteroscopic procedure without performing the resection, because of the risk on complications due to the hysteroscopy or anesthesia and possible pain complaints after the procedure.

Furthermore the HysNiche study will evaluate quality of life and sexual function in relation to complaints of spotting, which was not reported in earlier studies.

None of earlier studies reported on cost-effectiveness of a hysteroscopic niche resection compared to expectant management. We assume a hysteroscopic niche resection to be more cost-effective, since we expect it to prevent the need for invasive surgical interventions such as a hysterectomy due to therapy resistant spotting or menstrual pain. We expect postoperative recovery time to be short and medical consultation to be less frequent. And not irrelevant, we think quality of life could improve with the knowledge of having low health care costs.

Questionnaires used are not adjusted or validated for spotting complaints. Disease specific validated questionnaires have not been developed yet.

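### Random blocks of 2 and 4 within centre, in a trial of surgery versus no intervention, leave allocation partly predictable despite web-based concealment

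*Protocol article*

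**What the plan says.** The section on procedures, recruitment and randomisation states: "Randomisation will be performed by using ALEA, an online randomisation program". Allocation is made "with the use of permuted blocks with a random block size of 2 to 4 patients per block, stratified for participating centres". The comparison is hysteroscopic resection against no intervention.

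On recruitment, the same section says: "Eligible women will be informed about the study by one of the gynaecologists, residents or research nurse in the participating centre". Written consent comes before randomisation, and the niche is measured before study entry.

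Under Strengths and limitations the article says: "Randomisation is performed with the use of allocation concealment through a webbased randomisation program, which reduces the chance for bias". It then concedes: "The study is not blinded for the patient, which could possibly effect reported outcomes by the patient". It explains that a sham procedure was judged unethical. It does not discuss whether allocations can be predicted, and it does not say that block sizes are withheld from sites.

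The Statistical analysis section adjusts for relevant baseline values. It lists additional hormonal therapy, smoking and anticoagulation as potential confounders. Centre, the stratification factor, is not named.

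**The concern.** Concealment has two parts: nobody can look up the next allocation, and nobody can work it out from the past ones. A central web system secures the first. The second depends on block size whenever past allocations are visible. Here they are visible, because a woman in one arm has an operation and a woman in the other does not. The article mentions only the lack of patient blinding, but staff knowledge of past allocations follows from the nature of the arms. Stratifying by centre means that the sequence to be guessed is exactly the one that local staff observe.

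A recruiter who expects a particular arm could, knowingly or not, time or encourage consent accordingly. The trial plans only 100 women, and its primary outcome is the number of spotting days reported by unblinded women. A prognostic difference introduced at entry would pass into the treatment comparison. Baseline adjustment would remove only the part that is measured.

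**Working it through.** **Inputs from the article.** Permuted blocks of random size 2 to 4, stratified by centre; two arms of 50. Since blocks balance the arms, the usable sizes are 2 and 4.

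**Assumptions not in the article.** Sizes 2 and 4 are equally likely; 12 women per centre; the recruiter sees all past allocations in the centre but not the block boundaries.

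**The plan's own figure.** The article gives no figure for predictability. Its sample size reproduces: a difference of 2 days, SD 2.7, two-sided 5% and 90% power need 39.3, so 40 per arm by the t-test, and 40/(1 − 0.20) = 50. Block size does not enter this calculation.

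**Guessing rule.** Guess the arm that is behind in the centre; toss a coin if the totals are equal. Exact enumeration shows that this does as well as the optimal guess by someone who knows the block sizes.

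**Step 1: block boundaries.** Let u(k) be the probability that a block ends after woman 2k. Then u(0) = 1, u(1) = 0.5 and u(k) = 0.5·u(k−1) + 0.5·u(k−2), which gives 0.75, 0.625, 0.6875 and 0.6563 for k = 2 to 5.

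**Step 2: even-numbered women.** Before woman 2k the totals are always unequal.
- If a new block began with woman 2k−1, the lagging arm follows with probability 0.5·1 + 0.5·(2/3) = 5/6.
- Otherwise she is last in a block of 4, and the lagging arm is certain to follow.
- So P(correct) = 1 − u(k−1)/6.

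**Step 3: odd-numbered women.** Before woman 2k+1 the totals are equal unless she is third in a block of 4 whose first two went to the same arm. That has probability (1 − u(k))/3, and the lagging arm then follows with certainty. So P(correct) = 0.5 + (1 − u(k))/6.

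| Woman | P(correct) | Woman | P(correct) |
|---|---|---|---|
| 1 | 0.500 | 2 | 0.833 |
| 3 | 0.583 | 4 | 0.917 |
| 5 | 0.542 | 6 | 0.875 |
| 7 | 0.563 | 8 | 0.896 |
| 9 | 0.552 | 10 | 0.885 |
| 11 | 0.557 | 12 | 0.891 |

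The odd-numbered women sum to 3.297 and the even-numbered to 5.297, so the average is 8.594/12 = **71.6%**, against 50% by chance.

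**Step 4: certain allocations.** When one arm leads by two, the next two allocations are fixed for anyone who knows that no block exceeds 4. The expected number in 12 is 2·(0.1667 + 0.0833 + 0.125 + 0.1042 + 0.1146) = 1.1875, and 1.1875/12 = **9.9%**.

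**Step 5: how often a guess is informative.** Totals are unequal before (6 + 0.594)/12 = 55% of allocations. The lagging arm then follows in (5.297 + 0.594)/6.594 = 89% of them.

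**Step 6: alternatives, by exact enumeration at 12 women, sizes equally likely.**

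| Sizes | Correct | Certain |
|---|---|---|
| 2/4 (as stated) | 71.6% | 9.9% |
| 4/6 | 68.0% | 6.3% |
| 4/6/8 | 66.5% | 2.4% |
| 4 only | 70.8% | 33.3% |
| 2 only | 75.0% | 50.0% |

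**Sensitivity.** With 8 women per centre, sizes 2/4 give 71.4% and 9.4%. If size 2 is drawn two times in three, 12 women give 72.5% and 7.3%.

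**The case against.** The strongest reply is that the design already contains sensible safeguards and that the remedy buys little. The block size varies, which cuts certain allocations from 33% with fixed blocks of 4 to about 10%. Allocation is central. Eligibility rests on sonographic measurements made before entry, and consent precedes randomisation. The analysis adjusts for baseline. Larger blocks improve the overall guessing rate by only 4 to 5 percentage points. All of this stands, and it limits the severity. It does not remove the point, because a forecast can be formed before the next woman is approached. Consent before randomisation therefore narrows the room to act on it but does not close it.

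Several stronger readings are tempting and are not supported:

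- **That the next arm can usually be inferred.** In 45% of allocations the totals are equal and the rule is a coin toss. About 90% of allocations are not certain.
- **That the recruiter is often the surgeon.** The article names gynaecologists, residents or a research nurse as recruiters. It does not say who also operates, and several recruiters per centre make totals harder to track.
- **That the trial is biased, or that the concealment statement is false.** No selection is shown. The article claims only that concealment lowers the chance of bias, which is true; the statement is incomplete because it omits predictability.
- **That blocks of 3 are planned.** Under balanced allocation, 2 to 4 is naturally read as 2 and 4. The wording is loose, nothing more.

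**Conclusion.** The point holds as a property of the stated design: allocation within a centre is partly predictable, and web-based concealment does not prevent that. Its size is about 72% correct guesses and about 10% certain allocations, concentrated in the even-numbered women of each centre. These figures rest on the assumed equal probabilities and 12 women per centre, and they move little over the ranges tried.

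Whether anyone would act on a guess, and how far that would shift the result, cannot be derived from the document. Selection bias is a possibility, not a finding. Severity is minor to moderate.

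**What to change.** **If allocations remain to be made** (the article does not say):
- Have the randomisation unit choose block sizes at random from 4, 6 and 8. Of the two alternatives examined, this one clearly reduces certain allocations, from 9.9% to 2.4%; 4/6 reaches only 6.3%.
- Keep the new sizes out of documents that sites can see. This hinders identification of certain allocations. It does not stop the lagging-arm guess, which needs no knowledge of the sizes.
- Name centre as a covariate in the primary model, as it is the stratification factor and the Statistical analysis section does not list it. The analysis plan, which is not shown, may already do so. The number of centres is not given, so the form of the adjustment can be settled there.

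**If enrolment is complete:** qualify the concealment statement under Strengths and limitations. Say that small blocks within centre left allocation partly predictable to staff who knew earlier allocations.

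**Cost.** A setting in the randomisation system and a few sentences of text. The imbalance within a centre at any moment can reach half the largest block, so 4 women instead of 2. It is temporary within each block, except where a centre stops in mid-block, and centre adjustment addresses it. The target of 50 per arm does not change.
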